#### Decision-making

*Intention *is measured using 7 self-developed items regarding: breast self-examination; adherence to population mammography screening (above 50 years of age); breast screening by a physician every 6 months; mammography screening every year (own initiative); DNA testing; having a preventive breast operation (mastectomy); informing close relatives. Each item has a 7-point scale: 1 (definitely not) to 7 (definitely), and an additional category "not applicable".

*Behaviour *is measured by 6 items using a timeframe of "the last 6 months", regarding: breast self-examination; adherence to population screening; breast screening by a physician; mammography screening (own initiative); consulting a specialist about a preventive breast operation; preventive breast operation.

*Informed choice with regard to genetic testing*, which is based on knowledge, attitudes, genetic test uptake and value consistency, is assessed using a multi-dimensional measure of informed choice (MMIC) developed by Marteau [49] and extended by Van den Berg [50]. Attitudes towards having a DNA test for breast cancer is measured by two items with a 7-point rating scale ranging from 1 (bad) to 7 (good) and from 1 (useless) to 7 (useful). Genetic test uptake is measured at follow-up (T2/T1C and T3/T2C). To determine value consistency, attitude scores will be combined with test uptake [50].

*Difficulties in decision-making or decisional conflict *are measured by the Dutch version of the Decisional Conflict Scale (DCS) of O'Conner [51].

#### Evaluation of the intervention

The extent to which the additional risk information (intervention) is regarded as useful for decision-making, threatening, and easy to understand was assessed using a 7-point rating scale. Satisfaction with the information provided is measured by a 7-point response format, ranging from 1 (very dissatisfied) to 7 (very satisfied).

#### Personal experiences and characteristics

Several personal characteristics and experiences are measured which may have mediating effects on the efficacy of risk communication.

*Sociodemographic characteristics *included age, level of education, marital status, parent's country of birth, number of children, religious affiliation.

*Impact of family history *is measured using 4 self-developed items regarding: the number of family members that have or have had breast cancer (including the family relationship); perceived impact of this experience by a 7-point scale ranging from 1 (no strong impact) to 7 (very strong impact); the effect of this experience on perceived anxiety regarding getting breast cancer by a 7-point scale ranging from 1 (no strong effect) to 7 (very strong effect); the extent to which the subject "hereditary breast cancer" plays a part in the family by a 7-point scale ranging from 1 (not at all) to 7 (very).

*Severity of breast cancer *is measured by 6 items on the Consequences Subscale of the Dutch version for at-risk individuals of the Revised Illness Perception Questionnaire, that is IPQ-RAR [52].

*Perceived Personal Control *is measured by a Dutch translation of the Perceived Personal Control questionnaire (PPC) [53].

*Coping *is measured by the 19-item Utrecht Coping List (UCL) [54].

*General anxiety *is measured by a 20-item version of the Dutch version of the Trait scale (STAI-form Y) of the Spielberger State-Trait Anxiety Inventory (STAI) [55].

*Need for Cognition *can be described as an "individual disposition to engage in and enjoy thinking", and is measured by an 18-item Dutch version of the Need for Cognition Scale (NCS) [15].

*Cognitive ability *is measured using the 3-item Cognitive Reflection Test (CRT) [56].

*Decision-making style *is measured by the 22-item Melbourne Decision Making Questionnaire (Melbourne DMQ) [57].

*Social support *is measured by the 16-item Social Experiences Checklist (SEC) [58].

### Statistical analyses

Analyses will be performed to estimate the effect of the different interventions (formats) by comparing pre-test- (T0/T1) with post-test- (T2/T1C) outcome measures between the five different intervention groups and the control group, using multivariate analyses. At baseline (T0) and at T1 similar variables will be measured in order to be able to assess the effect of the regular counselling session with the genetic counsellor. Personal variables will be included as covariates. Repeated measures in MANOVA will be used to analyse changes over time and long-term effects (T3/T2C).

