**Figure 1 F1:**
[figure not shown]
Time planning of the intervention and questionnaires in the intervention group (conditions 1–5) and control group (condition 6).

During the additional consultation, risks are communicated in one of five ways (conditions), namely:

1) lifetime breast cancer risk in numerical format (in natural frequencies, i.e. X out of 100),

2) lifetime breast cancer risk in both numerical format and graphical format (i.e. population figures in 10 rows of 10),

3) lifetime breast cancer risk and age-related breast cancer risk in numerical format,

4) lifetime breast cancer risk and age-related breast cancer risk in both numerical format and graphical format, and

5) lifetime breast cancer risk in percentages.

Since the information given during the intervention not only differs from usual care regarding the format of the risks but also to the extent to which the information is structured, two control conditions are included. Condition 5, in which the risk is communicated in percentages as in the standard genetic counselling session (usual care), controls for the effect of giving risk information also in a structured way, enabling us to compare the effects of different risk formats. Condition 6, in which no intervention is given (usual care, henceforth defined as the control group) is used to control for the effect of repetition of the risk information (as compared to condition 5), and will control for Hawthorne effects [38].

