### Study population

Women with a family history of breast cancer who are first-time attendees applying for breast cancer counselling are invited to participate in the study. A family history of breast cancer is defined as having or having had at least one first-degree- and/or paternal second-degree family member with breast cancer. Women are considered ineligible if they are under 18 years of age, have evident psychiatric illness or terminal disease, and are unable to read and write Dutch. Women with a personal history of breast or ovarian cancer are also excluded, because of the complexities in risk counselling of women with a previous history of cancer. Participants are allocated into an intervention or control group (for randomisation procedure, see below). Stratification to first-degree family members is applied to ensure that all family members receive the same condition.

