### Procedure

Women applying for genetic breast cancer counselling are invited to participate by means of an information letter send to their home address. All participants provide written informed consent. In the intervention group, participants receive a self-administered questionnaire at four points in time (T0, T1, T2, T3), the control group receives this at three points in time (T0, T1C, T2C) (see Figure 1):

- T0 (baseline): The women will receive the first questionnaire at home before their first appointment with the genetic counsellor.

- T1 (after standard counselling session): A second questionnaire will be given after the standard genetic counselling session with the genetic counsellor and prior to the intervention (additional counselling with the risk counsellor).

- T2/T1C (2 weeks follow-up): A third questionnaire will be sent to the woman's home address at 2 weeks after the intervention, or a comparable point in time (control group).

- T3/T2C (6 months follow-up): The final questionnaire will be sent to the woman's home address.

A maximum of two reminders is sent to participants not returning their questionnaires. The three risk counsellors (one for each clinical genetics centre) who provide the intervention, have been specifically trained for this study. The intervention lasts for approximately 30 minutes. The risk counsellor is informed about the content of the previous standard counselling session by means of a "checklist after standard counselling", which the genetic counsellor fills in immediately after each session. This checklist includes information about the participant's risks e.g. individual estimated risk of getting breast cancer, also describing the risks formats that were used during counselling. When risks are not yet known, because, for instance, medical records need to be checked, intervention takes place after a second visit. Thus, enforcement of an intervention implies that in the genetic counselling session with the genetic counsellor at least the woman's breast cancer risk group (e.g. low, moderate, high) was communicated.

After the intervention, all participants receive a BRISC brochure in which risks are presented corresponding to the format of the intervention given.

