Some limitations of the BRISC study need to be addressed. This study aims at improving women's understanding of the risks, and we acknowledge that there are factors other than risk that can influence the decision-making process. In addition, although several precautions have been taken to achieve an optimal standardisation in counselling and procedures, interactive features must be acknowledged. Another limitation of this study is that it is not possible to blind the genetic counsellors completely because of the nature of the intervention. This applies to the intervention allocation and to the age-related formats due to anticipation of questions by the counsellee. Participants are informed that the BRISC study concerned different kinds of risk counselling and are blinded. Furthermore, although we would have preferred to test an integrated intervention in standard counselling sessions, it is not considered feasible, either ethically or practically, to have the intervention done in a structured way by the genetic counsellors themselves. If one of the formats proves to be most effective, this format could be integrated into the standard counselling session. Since members of the research team provided the additional consultations (interventions), implementation of a format in daily practice will need to receive further attention.

Finally, results may be extended to women with a personal history of cancer, other cancers, and also other diseases and settings, but further study would be required. Imprudent generalization should be avoided, although the BRISC study may provide an indication for risk communication in healthcare in general and cancer genetic counselling in particular.

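### The T0–T1 change is said to show the effect of regular counselling, but no group goes uncounselled, so it can only be described as a within-group change in conditions 1–5

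*Protocol article*

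**What the plan says.** The Statistical analyses section gives the reason for measuring the same variables at T0 and T1: "in order to be able to assess the effect of the regular counselling session with the genetic counsellor".

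The Procedure section fixes the timing:

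- T0: "The women will receive the first questionnaire at home before their first appointment with the genetic counsellor".
- T1: "A second questionnaire will be given after the standard genetic counselling session with the genetic counsellor and prior to the intervention".
- T2 in the intervention group, or T1C in the control group: "at 2 weeks after the intervention, or a comparable point in time (control group").

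T1 belongs to the intervention group only; "the control group receives this at three points in time (T0, T1C, T2C"). T1C is therefore the counterpart of T2, not of T1.

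The Intervention section places the additional consultation directly after the standard session and describes the comparator: "Condition 6, in which no intervention is given (usual care, henceforth defined as the control group"). Usual care is the standard session, so the control group is counselled too.

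Table 3 schedules the HADS and the PANAS at both T0 and T1. The Psychological well-being section gives their recall periods: the previous week for the HADS and the previous few days for the PANAS.

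**The concern.** An effect of the regular session is a contrast between having it and not having it at the same point in time. Nobody in this trial goes without it. What the plan observes is each woman's change from a questionnaire sent to her home to one handed over after the appointment. Several things change together with counselling:

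- time has passed and the awaited appointment is over;
- the same instruments are being answered a second time;
- the setting has moved, by inference from home to clinic;
- women who applied while unusually worried may be drifting back to their own level.

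Two features make the reading weaker still. Where T1 follows the session on the same day, a HADS or PANAS answer refers mainly to days before the session took place. And T1 is seen only in women who are about to have an extra consultation. The Discussion concedes that the genetic counsellors cannot be fully blinded: "This applies to the intervention allocation and to the age-related formats due to anticipation of questions by the counsellee". The session observed at T1 may therefore differ somewhat from counselling given alone.

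At stake is a causal statement about regular counselling, covering perceived risk, worry, anxiety and mood, that the design cannot back.

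**Working it through.** **1. Is there a comparator?** Conditions 1–5 have the standard session, then T1, then the additional consultation. Condition 6 has the standard session and then T1C, at the time of T2. No group is uncounselled, and no group outside conditions 1–5 has a measurement at T1. Adding T1 to condition 6 would not help, because those women are counselled as well.

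**2. What period does T1 cover?** The additional consultation follows the standard session directly, and T1 falls between the two. On a single visit, T1 is completed within a short time of the session. A recall period of a week (HADS) or a few days (PANAS) then lies almost wholly before it. When risks are not yet known, the Procedure section moves the intervention to a second visit, so the T0–T1 interval may also differ between women.

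**3. How many women?** The Sample size section gives 60 per condition and a 20% drop-out rate. Its total reproduces: 6 × 60 = 360, and 360 / (1 − 0.20) = 450. Conditions 1–5 then supply 5 × 60 = 300 women.

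**4. How small a drift is significant?** For a paired comparison in SD units, SE = √(2(1 − r)/n), and the smallest significant mean shift is 1.96 × SE at the plan's two-sided 0.05. The T0–T1 correlation r is not in the documents, so it is assumed over a range.

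| r (assumed) | SE, n = 300 | Significant shift | P(significant), drift 0.10 SD | P(significant), drift 0.15 SD |
|---|---|---|---|---|
| 0.5 | √(1.0/300) = 0.0577 | 0.113 SD | 0.41 | 0.74 |
| 0.7 | √(0.6/300) = 0.0447 | 0.088 SD | 0.61 | 0.92 |
| 0.8 | √(0.4/300) = 0.0365 | 0.072 SD | 0.78 | 0.98 |

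The probabilities are Φ(δ/SE − 1.96) + Φ(−δ/SE − 1.96), where δ is a drift that has nothing to do with counselling. The drift sizes are illustrations, not estimates. If nearly all recruited women complete T1 (5 × 75 = 375), the significant shift falls to 0.064–0.101 SD for r from 0.8 to 0.5.

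**5. What can be said of regression to the mean?** If selection lifts the T0 mean by k SD above the women's usual level, the expected fall is k(1 − r). The documents do not give k. At k = 0 the rejection rate is the nominal 0.05 (0.051 in simulation at r = 0.7). At k = 0.3 it is 0.74, 0.52 and 0.38 for r = 0.5, 0.7 and 0.8. The source of the selection also matters. In simulation at r = 0.7, selecting women on an earlier occasion whose transient error is independent of T0 gave 0.044, whereas selecting on T0 itself above 1 SD gave 1.00.

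**The case against.** The best case for the plan has four parts.

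- **It is a side remark.** None of the four research questions concerns the regular session, and the sentence names no dedicated test or hypothesis. A condensed article may leave the caveats to the full protocol. This stands as a limit on importance. It does not rescue the sentence, which states a causal purpose, and no later document can supply the missing comparator.
- **Regression to the mean is not shown.** A reader might infer that regression to the mean alone would produce a significant effect. The documents do not support that. Eligibility is defined by family history and first attendance ("Women with a family history of breast cancer who are first-time attendees applying for breast cancer counselling"), with no threshold on worry, anxiety, perceived risk or any T0 score. The Discussion allows for self-selection but says nothing about transient concern at T0. This objection stands in full: regression to the mean is one possible contributor of unknown size, and zero is among its possible values.
- **The 300 women are not fully independent.** Allocation is by condition round within centre. Correlation within rounds or counsellors would widen the SE and raise the shift needed for significance. This stands as a caveat on the 0.07–0.11 SD. It does not remove the confounding.
- **Some of this is disclosed.** Incomplete blinding is listed as a limitation, and usual care is standardised by agreement and checklists. That is true, but standardising the session does not provide an uncounselled comparison.

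**Conclusion.** The point holds as a minor one. T0–T1 is an uncontrolled within-group change in conditions 1–5 and cannot identify an effect of the regular session. It is least interpretable for the HADS and the PANAS because of their recall periods. The size of the bias is unknown. What can be said is that with 300 women a drift of about 0.07 to 0.11 SD from any source would reach significance, given an assumed correlation of 0.8 to 0.5 and independence between women. A significant T0–T1 change would therefore say little about its cause.

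Two stronger readings go beyond the documents. One is that regression to the mean by itself will create the effect; this needs an elevation at T0 that is nowhere stated. The other is that the trial's main results are compromised. They are not, on this point: the comparisons between formats have conditions 5 and 6 as controls and do not depend on a causal reading of T0–T1.

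**What to change.** In the Statistical analyses section, change the stated purpose of the T0 and T1 measurements so that they serve to *describe the change around* the regular counselling session in conditions 1–5. Add that no causal conclusion will be drawn from T0–T1, least of all for the HADS and the PANAS, whose T1 answers mostly refer to the period before the session. Keep T1 as the pre-intervention value for contrasts within conditions 1–5, a use the section already allows.

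The cost is the wording of one paragraph and the loss of one side claim. Data collection, sample size and the format comparisons stay as they are.

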### Objectives and research questions

The main objective of the present study is to evaluate the effects of different formats of risk communication on the counsellee's understanding and perception of the risk (cognitive outcomes), psychological well-being, and decision-making. In particular, we aim to investigate numerical versus graphical risk formats and lifetime breast cancer risks versus age-related risks. The research questions are:

1) What is the effect of the addition of a graphical format to standard risk information on cognitive outcomes, psychological well-being, and decision-making?

2) What is the effect of the addition of an age-related format to standard risk information on cognitive outcomes, psychological well-being, and decision-making?

3) What is the effect of the combination of both the addition of a graphical format and the addition of an age-related format on outcomes compared to research questions 1 and 2 (i.e. effect modification/interaction)?

4) How do the counsellee's personal experiences and characteristics mediate the effect on the communication of risk?

This article describes and discusses both the design and the content of the intervention of the BRISC (Breast cancer RISk Communication) study, a multicentre controlled clinical trial, to optimise the communication of breast cancer risks in genetic counselling among women with a family history of breast cancer.

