**Personal characteristics**						
Sociodemographic characteristics		X				
Impact of family history				X	X	
Severity of breast cancer	IPQ-RAR			X	X	
Perceived Personal Control	PPC	X		X	X	X
Coping	UCL					X
General anxiety	STAI-trait			X	X	
Need for cognition	NCS			X	X	
Cognitive ability	CRT					X
Decision-making style	Melbourne DMQ					X
Social support	SEC			X	X	

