## Discussion

Understanding risks is considered to be crucial for informed decision-making. However, inaccurate risk perception is a common finding in women attending genetic counselling regarding breast cancer. Although the literature provides recommendations for the use of frequencies, graphical displays and short-term risks such as age-related risks (i.e. risks for the next ten years) in risk communication, these recommendations are based primarily on research using hypothetical scenarios. In addition, the recommended approaches are not generally used in standard care. The BRISC study is designed to fill the gaps with an evaluation of the effects of different formats of communicating risks to counsellees facing real decisions in a clinical setting. Results will be used to improve risk communication in order to stimulate informed decision-making among women with a family history of breast cancer.

The BRISC study is a field study; in other words, a clinical trial which offers a unique opportunity to evaluate effects of different formats of communicating risks to counsellees facing decisions such as informing relatives who may also be at risk, whether and when to start mammography screening, and, assuming eligibility, whether to test for mutations in *BRCA1/2*.

Quantitative outcome measures are collected using questionnaires at four points in time. The follow-up questionnaire is sent 6 months after the intervention, thereby enabling medium-term effects to be detected. With this comprehensive collected data, it will be possible to clarify the various effects of different formats on four dimensions evaluating the effectiveness of the risk communication process. It is not inconceivable to expect that some formats have positive effects on one of the dimensions and negative effects on another dimension. Additionally, the outcomes of this project will give a better understanding of who, for example, as a function of cognitive capacity, might or might not benefit from different formats.

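### Eight of the ten personal characteristics are first measured after the intervention, so those the consultation can change should not be covariates in the format contrasts

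*Protocol article*

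**What the plan says.** The Statistical analyses section compares T0/T1 with T2/T1C outcomes across the five intervention conditions and the control group, and adds: "Personal variables will be included as covariates". It does not say which variables, or which measurement of each.

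Research question 4 asks: "How do the counsellee's personal experiences and characteristics mediate the effect on the communication of risk". The section on personal experiences and characteristics gives the same role: "Several personal characteristics and experiences are measured which may have mediating effects on the efficacy of risk communication". The Discussion words the aim differently. It expects the results to show "who, for example, as a function of cognitive capacity, might or might not benefit from different formats".

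Table 3 fixes when each characteristic is collected. For example, the row "Impact of family history" is marked only at T1C and T2. According to the Procedure section, T2/T1C falls two weeks after the intervention, or at a comparable time for controls. The last form is "T3/T2C (6 months follow-up): The final questionnaire will be sent to the woman's home address".

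**The concern.** A covariate in a treatment-effect model should not itself be affected by treatment. If it is, adjustment removes or distorts the part of the effect that runs through it. The sentence on covariates admits every personal variable, yet most are collected only after the consultation whose effect is being estimated.

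The protocol's own Background makes such movement plausible for some of them. It reports that pictographs carried more affective weight than numbers, and that overestimated risk goes with worry. Answers given two weeks later about how severe breast cancer is, or how far family experience raises anxiety, could therefore differ by format. The contrasts exposed are those of research questions 1 and 2, on risk perception, the primary outcome.

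There is a second, smaller mismatch. Who benefits from a format is a question of effect modification, and a covariate term alone estimates neither modification nor mediation.

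**Working it through.** **1. Timing, counted from Table 3 (columns T0, T1, T1C, T2, T3/T2C)**

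| First measured | Characteristics | Number |
|---|---|---|
| T0 | sociodemographics; Perceived Personal Control (repeated later) | 2 |
| T1C/T2, two weeks | family-history impact; severity; trait anxiety; need for cognition; social support | 5 |
| T3/T2C, six months | coping; cognitive ability; decision-making style | 3 |

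So 5 + 3 = 8 of 10 have no pre-intervention value. None is collected at T1, the last form before the intervention. Perceived Personal Control is safe only if its T0 value is used.

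**2. Which of the eight can move**

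- Plausibly moved by risk counselling: perceived severity, perceived impact of family history and its effect on anxiety, and possibly trait anxiety.
- Dispositional, likely to move little: need for cognition, coping, decision-making style, cognitive ability.
- Fixed: the number of affected relatives, which is one of the four family-history items.
- Social support: nothing in the document suggests that the consultation changes it.

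**3. Size of the distortion (assumed values; the document gives none)**

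Let a be the shift in the covariate caused by the format (in SD) and b the covariate's slope on the outcome. With no unmeasured common cause of covariate and outcome, adjusted effect = total effect − a × b. Take a total effect of 0.50 SD. This is close to what 60 per group can detect: (1.960 + 0.842) × √(2/60) = 0.51 SD at 80% power and two-sided 5%.

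| Shift a | b = 0.3 | b = 0.5 |
|---|---|---|
| 0 | 0.50 | 0.50 |
| 0.1 | 0.47 | 0.45 |
| 0.3 | 0.41 | 0.35 |
| 0.5 | 0.35 | 0.25 |

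For example, 0.50 − 0.3 × 0.5 = 0.35. Simulation agrees to within 0.01. If a × b is negative, the adjusted effect is too large instead. Between two intervention formats, only the difference in shift counts.

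**4. Loss of women through six-month covariates**

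The plan's inflation reproduces: 6 × 60 = 360, and 360 / (1 − 0.20) = 450, or 450 / 6 = 75 per condition. If all drop-out fell between two weeks and six months, and the analysis used complete cases, a two-week model with a six-month covariate would keep 75 × 0.80 = 60 and lose up to 15 per condition. If drop-out falls earlier, the loss caused by the covariate is smaller.

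**5. Research question 4**

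In simulated data with an average format effect of 0.30 and a format-by-characteristic interaction of 0.40, a model with the covariate as a main effect returns 0.30 and no estimate of the interaction. Adding the product term returns 0.39 for it.

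**The case against.** The strongest reply has three parts.

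- **Most late variables are traits.** The protocol describes need for cognition as a disposition and refers to dispositional coping patterns. Trait anxiety has its own scale, separate from state anxiety. A 30-minute consultation does not change how many relatives were affected. A reader might infer from the count of eight that all eight bias the contrasts. The documents do not support that: late measurement biases only where the variable responds, and the table shows no distortion at zero shift.
- **The sentence is condensed.** It does not say that all ten variables enter every model, or that six-month variables enter the two-week model; the same section also covers the six-month analysis. A reader might infer that research question 4 gets no answer at all. That goes too far. The article says covariates, not main effects only. It also names no interaction for research question 3, which it defines as an interaction, so interactions may well be left to a fuller plan.
- **The loss of women is a worst case.** The document gives neither the timing of drop-out nor a complete-case rule, and 60 per condition is the number the sample-size section requires.

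All three limit the size of the problem. They do not remove it. Table 3 fixes the timing, which no later analysis plan can change for data already collected, and the covariate sentence sets no restriction.

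**Conclusion.** The point holds in a limited form and should be corrected. Followed as written, the covariate sentence permits adjustment of the format contrasts for variables that the consultation can change. The timing count (8 of 10) is certain. The distortion is a risk confined mainly to perceived severity, the perceived-impact and anxiety items, and possibly trait anxiety. Its size cannot be derived from the document: it runs from zero to half of a 0.50 SD effect over the assumed range. The loss of up to 15 of 75 women per condition depends on complete-case analysis and on all drop-out falling after two weeks.

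On research question 4, the supportable statement is narrow. The protocol speaks of mediation while the Discussion describes moderation, and the one stated use of these variables tests neither by itself.

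**What to change.** - In the primary effect models, adjust only for pre-intervention variables: the T0 outcome value (T1 is not collected in the control group), sociodemographics, T0 Perceived Personal Control, and the risk group recorded on the form that the genetic counsellor completes after the standard session. Confirm that this form is also completed for control women, since the article describes it as informing the risk counsellor.
- Fixed facts, such as the number of affected relatives, may be kept although they are collected late.
- Do not adjust for other characteristics first measured at T2/T1C or T3/T2C.
- Address research question 4 with format-by-characteristic interactions and describe it as moderation. Label interactions with characteristics measured at two weeks or six months as exploratory; this includes cognitive ability, the Discussion's own example.
- Do not move instruments to T0 during the trial. Conditions rotate by round, so measurement timing would then differ by condition. By Table 2, a change at month 11 would put all three rounds of condition 4 on the new schedule, but only one of three for conditions 1 and 2.

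The cost is a change of wording and slightly less covariate precision. No new data are needed.
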